**Figure 1 F1:**
[figure not shown]
The flow chart of the study.

**Table 1 T1:** Study assessments, procedures and timetable

**Assesment**^**1**^	**Telephone interview**	**Baseline visit**	**3-month visit**	**9-month visit**	**At 24 months**
Patient					
Inclusion criteria	X				
Demographics, diagnoses, drugs, background information		X	X	X	
CDR, MMSE, verbal fluency, clock drawing test		X	X	X	
Grip strength, blood pressure and pulse		X	X	X	
MNA		X	X	X	
Weight, BMI		X	X	X	
ADL, IADL		X			
Cornell Depression Scale		X	X	X	
Illness Cognition Questionnaire		X	X	X	
15D QoL		X	X	X	
Use of health and social services, mortality			X	X	X
Psychosocial well-being scale		X	X	X	
Spousal caregiver	X	X	X	X	
Demographics, diagnoses, drugs, questions related to coping with dementia		X	X	X	
Psychosocial well-being scale		X	X	X	
Grip strength, blood pressure and pulse		X	X	X	
Weight, BMI		X	X	X	
Sense of competence, SCQ		X	X	X	
CES-D		X	X	X	
12-GHQ		X	X	X	
Pearlin Mastery Scale		X	X	X	
Rand-36 QoL		X	X	X	
Use of health and social services, mortality			X	X	X

^1^*CDR* Clinical Dementia Rating Scale
[23] (0.5 suggests possible dementia, 1 mild, 2 moderate, and 3 severe dementia), *MMSE* Mini Mental State Examination
[24]. *MNA* Mini Nutritional Assessment
[29] (<24 suggests risk for malnutrition or malnourishment); *BMI* body mass index; *ADL* activities of daily life
[27]; *IADL* instrumental activities of daily living
[28]; Cornell Depression Test
[30]; Illness Cognition Questionnaire
[31]; 15D QoL, measure of health-related quality of life
[22]; Psychosocial Well-being Scale
[33]; *SCQ* Sense of Competence Questionnaire -
[39]; *CES-D* The Center for Epidemiologic Studies Depression Scale
[37]; 12-*GHQ*, 12-item General Health Questionnaire. Pearlin Mastery Scale
[38];Rand-36 QoL
[34,35].

### Intervention

Group facilitators visit the couples prior to the group rehabilitation in order to get acquainted with them, and to encourage them to express their wishes and preferences for topics for the group sessions. The groups of 10 participants meet once a week for eight weeks. Patients and spousal caregivers will meet their peers in their own groups concurrently. The group meetings last for four hours including lunch, taxi transportation will be provided. Both groups are facilitated by two trained professionals, and the content of the sessions varies according to participants’ preferences. They may include, for example, topics on dementia and prevention of further cognitive decline, active lifestyle and emotional well-being, spousal relationship, future planning and community services. Participants are also advised to collect a folder of important information and tips to overcome difficulties with dementia. Couples are encouraged to define their individual goals for dementia care. Dementia patients having Cornell scale
[30] points > 10, and caregivers having CES-D
[37] points > 20, or suffering from significant burden are offered a geropsychiatric consultation (EH).

Groups work on the basis of the psychosocial group rehabilitation model described earlier
[33,40] and on self-management supporting principles
[5,19]. They are based on a constructive learning theory and a reflective learning model, in which self-management skills are built little by little during the intervention. Different kinds of active learning methods are used in the groups, like working in pairs and brainstorming sessions. Group intervention is goal-oriented and it takes advantage of group dynamics and peer support. The aim is to enhance the active agency of older people, to empower them, and to increase their feelings of self-efficacy and mastery. The intervention is tailored according to the wishes of group participants. It, for example, provides participants with knowledge (about, for example, dementia, active lifestyle, nutrition) and skills (for example problem solving and control of everyday family life, goal setting) and so strengthens their coping skills.

Facilitators receive training for group facilitation (the ‘Circle of Friends’ model)
[41] and they receive tutoring through the group facilitating process. Facilitators write diaries of the group meetings that enable the researchers to follow and tutor the group activities. In addition, some group meetings are observed by researchers and facilitators receive constructive feedback.

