### Statistical analyses

Sample size was calculated based on the 15D measure
[22]. With an estimated standard deviation of 0.10, and type I error of 5%, and 80% power, 62 patients would be needed in each group to show a 10-point difference between groups. We estimated that 20% will drop out so we decided on 160 patients as a sample size. Data will be analyzed on an intention-to-treat basis. In baseline findings, the continuous variables and descriptive values will be expressed by means with standard deviations (SD) and medians with range. For the variables with a normal (Gaussian) distribution, statistical comparisons between the groups will be made by using an analysis of variance. If the variables have a non-normal distribution or ordinal level, statistical comparison between groups will be made using the Mann–Whitney U test. Measures with a discrete distribution will be expressed as percentages (%) and analyzed by chi-square or Fischer's exact test when appropriate. Imputation method of ‘the last observation carried forward’ (LOCF) and ‘worst-rank score’ principle will be used.

Since the distributions of health care costs are highly skewed, the differences between means and confidence intervals are estimated using the bootstrap method (bias corrected and accelerated bootstrapping).

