There are also challenges in this study. The population is old and frail with comorbidities and, therefore, prone to competing causes of complications and death. The intervention is delivered in a multifactorial and flexible format, so it is difficult to determine which aspects of intervention are efficacious. It is possible that there is heterogeneity in the continuation of meetings with group members after the eight weeks of organized meetings, which, with dropping out, may contribute to insufficient difference between the intervention and normal care groups. Contamination of the control group presumably is not a problem, because psychosocial group rehabilitation is rarely available for dementia patients and their caregivers in Finland. It is also challenging to know if the selected scales are suitable and sensitive to measure changes in self-efficacy, mastery, competence and especially HRQoL and depression in this heterogeneous group consisting of various stages of dementia.

The group dynamics and atmosphere are unique in each group. It may be possible that the dementia patient is happy in their group, but the caregiver feels burden or bored in their own group and, therefore, wishes to drop out of the intervention. It is important that the group leaders communicate with each other to know how the ‘other spouse’ works in the other group.

The trial follows common ethical principles in randomized trials. Participants are not exposed to risks, they receive verbal and written information before any study procedures, they participate voluntarily, and they may withdraw at any phase of the study. Individuals with dementia write an informed consent when they are capable of doing so; otherwise the spousal caregiver writes it on behalf of both of them. Control group members receive normal care offered by community. For the rehabilitation and study nurse visits, a risk/liability insurance is taken for participating dyads.

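### The sample size and the named tests make no allowance for treatment in about eight facilitated groups, so false-positive rates can exceed 5% and 80% power is not assured

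*Protocol article*

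**What the plan says.** Study procedures (protocol article, Methods) has couples randomized in batches of 20, half to each arm. The Abstract puts 80 of the 160 in the intervention. Under Intervention, "The groups of 10 participants meet once a week for eight weeks"; patients and spouses meet separately but at the same time, each group has two facilitators, and session content follows what its members prefer. The same section names group dynamics and peer support as working parts of the programme, and the Discussion says "The group dynamics and atmosphere are unique in each group". Controls receive usual community care and are not grouped.

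Under Statistical analyses, "Sample size was calculated based on the 15D measure". The inputs are: "With an estimated standard deviation of 0.10", a 5% type I error, and "80% power, 62 patients would be needed in each group", for a difference printed as ten points. The total is then raised to 160 for 20% dropout. No ICC or design effect is among these inputs. For normally distributed variables, "statistical comparisons between the groups will be made by using an analysis of variance"; Mann-Whitney, chi-square or Fisher tests cover the rest. For costs, "differences between means and confidence intervals are estimated using the bootstrap method" (bias-corrected and accelerated). No named method has a term for the facilitated group.

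**The concern.** Members of one intervention group share facilitators, jointly chosen topics and each other's company for eight weeks. The article treats this shared experience as part of how the programme works and as different from group to group, so it is inconsistent to assume zero correlation within groups. Because only the intervention arm is grouped, the design is partially nested.

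A test that assumes independence uses too small a variance for the intervention mean. Confidence intervals are then too narrow and the false-positive rate exceeds its nominal level. This applies to all three primary outcomes (patients' 15D, caregivers' RAND-36 and SCQ), since both members of the couple attend groups. The planned power is also calculated for more information than the design supplies.

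**Working it through.** **Inputs from the article.** SD 0.10; type I error 5% (two-sided assumed); power 80%; 62 per arm; 20% dropout; 160 randomized 1:1; groups of 10.

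**Derived.** 80/10 = 8 patient groups and 8 parallel caregiver groups. After dropout, 160 × 0.8 = 128, or 64 per arm and 64/8 = 8 per group.

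**Assumed.** ICC 0.01, 0.05 and 0.10, because none is stated; total SD held at 0.10.

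**Step 1: reproduce 62 per arm.** n = 2(1.96 + 0.842)² × SD²/δ².

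- δ = 0.10: 2 × 7.85 × 0.01/0.01 = 15.7, so 16 per arm. This does not give 62.
- δ = 0.05: 2 × 7.85 × 0.01/0.0025 = 62.8, close to 62. Solving back from 62 gives δ = 0.0503. Then 63/0.8 = 79 per arm, which fits 160.

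So 62 is an independence calculation at a standardized difference of 0.5. The value 0.05 is back-solved and is not printed.

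**Step 2: variance under partial nesting.** Design effect in the intervention arm: DE = 1 + (m − 1) × ICC, where m is group size. With equal arms, the true variance of the difference divided by the independence variance is R = (DE + 1)/2.

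- Type I error of the independence test = 2[1 − Φ(1.96/√R)].
- Power at δ = 0.05 = Φ(0.5/√(2/n)/√R − 1.96).

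The last column uses a non-central t with Satterthwaite degrees of freedom for eight intervention groups (between 15.9 and 23.9).

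| n per arm, m | ICC | R | SE understated by factor √R | Type I error | Power, normal | Power, 8-group df |
|---|---|---|---|---|---|---|
| 64, 8 | 0.01 | 1.035 | 1.017 | 5.4% | 79.4% | 76.0% |
| 64, 8 | 0.05 | 1.175 | 1.084 | 7.1% | 74.2% | 69.9% |
| 64, 8 | 0.10 | 1.350 | 1.162 | 9.2% | 68.2% | 63.1% |
| 80, 10 | 0.01 | 1.045 | 1.022 | 5.5% | 87.1% | 84.3% |
| 80, 10 | 0.05 | 1.225 | 1.107 | 7.7% | 81.5% | 77.4% |
| 80, 10 | 0.10 | 1.450 | 1.204 | 10.4% | 74.7% | 69.3% |

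With no clustering, power at 64 per arm is 80.7% and at 80 per arm 88.5% (normal approximation). Power drops below 80% at an ICC of about 0.006 with 64 per arm, and about 0.06 with 80 per arm.

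**Step 3: simulation check of the type I error.** An ordinary t-test with eight intervention groups and 40,000 runs per setting gave 5.4%, 6.8% and 9.3% at m = 8, and 5.5%, 7.8% and 10.2% at m = 10. These agree with the formula.

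**Step 4: if 0.10 was intended.** Power stays above 99% in every row. The type I errors do not change, because they do not depend on δ.

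**The case against.** **The outcome model may not be fixed here.** The test list follows a sentence that opens with baseline findings, and a full analysis plan may exist. A reader might go the other way and infer that every published interval will be too narrow; the article does not establish that. But the test sentences sit between the intention-to-treat statement and the imputation rules (last observation carried forward, worst rank), which make sense only for follow-up data. They are also the only non-cost tests given. The sample size is stated in full and cannot be read as deferred.

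**The power loss is conditional.** It is tempting to say that 80% power is not delivered. The documents do not support that: no ICC is given, 0.05 is back-solved, and a difference of 0.10 leaves ample power. The plan is intention-to-treat with imputation, so analysing all 80 per arm is a relevant case, and there power holds above 80% up to an ICC of about 0.06 by normal approximation. At an ICC of 0.01 the effect on error and power is small. Tutoring of facilitators towards uniform quality may keep the ICC low. All of this stands.

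**Individual allocation limits the type I argument.** If the programme changed nobody's outcome and groups had no influence, it would create no correlation. Inflation needs group effects that vary around a zero mean. That condition stands, but group effects that differ are what the Discussion describes.

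**Randomization in batches of 20.** The article calls these batches clusters, so a reader might infer a cluster-randomized trial and apply a design effect to both arms. Couples are allocated individually within each batch, so that does not follow. Each intervention group of ten appears to have ten concurrent controls, and similarity shared across a batch cancels in the comparison. Ignoring it alone is slightly conservative: at an assumed batch ICC of 0.05, R = 0.95 and the error is 2[1 − Φ(1.96/√0.95)], about 4.4%. Only the group-specific part inflates error, and the remedy must separate the two.

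**The cost bootstrap.** A reader might infer that individuals are resampled. The article does not state the resampling unit, so this needs specifying but is not a demonstrated error.

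**Conclusion.** The point holds in conditional form. The sample size contains no allowance for grouping in the intervention arm, and the named tests assume independence. For any positive group-specific ICC those tests understate the standard error, by 2% to 16% at 8 per group and 2% to 20% at 10 per group for ICC 0.01 to 0.10. The two-sided error is then 5.4% to 9.2%, or 5.5% to 10.4%. This rests on the named tests being used for outcomes and on the assumed ICC range, but not on the target difference.

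The 80% power is not assured. It also depends on the target difference being about 0.05, and the printed ten points must first be reconciled with an SD of 0.10 and 62 per arm.

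**What to change.** 1. Analyse each outcome with a partially nested mixed model: a random effect for facilitated group in the intervention arm only, a term for the randomization batch of 20, and Kenward-Roger or Satterthwaite degrees of freedom. Use patient groups for patient outcomes and caregiver groups for caregiver outcomes.
2. State the bootstrap's resampling unit for costs, and resample whole intervention groups.
3. State the target 15D difference in the same units as the SD. Then restate power at N = 160 for an ICC range such as 0.01 to 0.10, with and without 20% dropout, using degrees of freedom that reflect eight groups.
4. Record group membership and batch for every couple in the analysis data set.

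The cost is wording and analysis effort, slightly wider intervals and a slightly lower stated power. No extra patients are needed. With only eight groups the group variance will be estimated imprecisely, which is why the small-sample degrees of freedom matter.

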### Outcome measurements

Primary outcome measures are changes in patients’ HRQoL assessed by 15D
[22] and in spousal caregivers’ HRQoL assessed by RAND-36
[35], sense of competence assessed by SCQ
[39]. Secondary outcome measures are patients’ time spent at home and changes in patients’ depression (Cornell)
[30], and feelings of acceptance and helplessness assessed using subscales of the Illness Cognition Questionnaire
[31] and cognition (verbal fluency, the clock drawing test (CDT))
[25,26]. Secondary outcome measures for caregivers are psychological well-being assessed by 12-GHQ
[36] and personal coping resources by the Pearlin Mastery Scale
[38] and also changes in depression will be measured by CES-D
[37]. Weight, blood pressure and hand grip are measured as secondary outcomes in the couples. Total mortality, use and costs of health care and social services of both spouses as well as cost-effectiveness of the intervention are measured up to 24 months from the beginning of the baseline measurements.

The study is made in co-operation with the Health Care Centre and Social Services Department of the City of Helsinki, the University of Helsinki, the Central Union for the Welfare of the Aged, and the Rehabilitation Hospital of Oulunkylä.

### Statistical analyses

Sample size was calculated based on the 15D measure
[22]. With an estimated standard deviation of 0.10, and type I error of 5%, and 80% power, 62 patients would be needed in each group to show a 10-point difference between groups. We estimated that 20% will drop out so we decided on 160 patients as a sample size. Data will be analyzed on an intention-to-treat basis. In baseline findings, the continuous variables and descriptive values will be expressed by means with standard deviations (SD) and medians with range. For the variables with a normal (Gaussian) distribution, statistical comparisons between the groups will be made by using an analysis of variance. If the variables have a non-normal distribution or ordinal level, statistical comparison between groups will be made using the Mann–Whitney U test. Measures with a discrete distribution will be expressed as percentages (%) and analyzed by chi-square or Fischer's exact test when appropriate. Imputation method of ‘the last observation carried forward’ (LOCF) and ‘worst-rank score’ principle will be used.

Since the distributions of health care costs are highly skewed, the differences between means and confidence intervals are estimated using the bootstrap method (bias corrected and accelerated bootstrapping).

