### Study procedures

The baseline visit lasts about one hour and includes interviews of both spouses and collection of demographic data, diagnoses, current medications, and baseline use of health and social services. Diagnoses and medications are confirmed from medical records provided by the couples. Charlson’s comorbidity index is calculated to assess the severity and prognostic value of the participants' disease burden
[21].

Health-related quality of life (HRQoL) of the patients is assessed by using the 15D instrument
[22]. Dementia patients are also assessed with the Clinical Dementia Rating Scale (CDR)
[23], the Mini Mental State Examination (MMSE)
[24], verbal fluency
[25], and the clock drawing test
[26]. Other measurements include activities of daily living (ADL)
[27], instrumental activities of daily living (IADL)
[28], the Mini Nutritional Assessment (MNA)
[29], Cornell depression test
[30], Illness Cognition Questionnaire
[31], frailty criteria
[32], and the Psychosocial Well-being Scale
[33]. The presence of advance directives, such as a living will, are inquired about. Clinical measurements include height, weight, blood pressure and hand grip strength.

The spousal caregivers are asked questions concerning the impact of their spouse’s dementia diagnosis and they are assessed by the RAND-36 HRQoL instrument
[34,35], 12-item General Health Questionnaire (GHQ-12)
[36], the Center for Epidemiologic Studies Depression Scale (CES-D)
[37], Pearlin Mastery Scale for their personal coping resources
[38], and the Sense of Competence Questionnaire (SCQ)
[39]. Their weight and blood pressure is also assessed on each visit.

The couples are randomized in clusters of 20. After acquiring informed consent to the study and assessing 20 couples with eligibility criteria, the randomization is performed by telephone to a randomization center. Couples are randomly allocated by means of computer-generated random numbers. Every randomization result will appear in the program after the participants name has been written and the person executing the randomization has confirmed the process with her initials. This ensures that neither the study nurse, nor person doing the randomization can influence the result. Half of the participants are randomized to the rehabilitation group (intervention group) and the other half receives usual care (control group).

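### The sample-size inputs contradict each other: with an SD of 0.10, 62 per group does not match a 10-point 15D difference on any reading

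*Protocol article*

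**What the plan says.** The only powering statement is in the Statistical analyses section of the protocol article. It names the outcome ("Sample size was calculated based on the 15D measure"), then the assumptions ("With an estimated standard deviation of 0.10, and type I error of 5%, and 80% power"), then the result: "62 patients would be needed in each group to show a 10-point difference between groups". It then allows for attrition: "We estimated that 20% will drop out so we decided on 160 patients as a sample size". Allocation is 1:1 (Study procedures), with 80 couples per arm (Abstract, Methods). No section says what one point on the 15D is, and none gives a second target difference or a second SD. The Outcome measurements section lists the 15D as one of three primary measures; the other two, RAND-36 and SCQ, have no power statement.

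**The concern.** The SD is given as a decimal and the target difference as a whole number of points, so the two are not visibly on one scale. The usual charitable step, reading 10 points as 0.10, makes the target equal to one SD, and a one-SD difference needs far fewer than 62 per group.

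The target difference tells a reader what a null result can exclude. A reader who takes it as 0.10 with the printed SD would believe the trial was sized for an effect twice as large, in SD units, as the one 62 per group fits. A non-significant result would then be judged against a target that does not belong to this sample size. The Discussion itself doubts whether the chosen scales are sensitive enough, HRQoL in particular, so the intended target should be legible.

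**Working it through.** **Inputs.** SD 0.10, type I error 5%, power 80%, 62 per group, 20% dropout and 160 in total (all from Statistical analyses); 1:1 allocation (Study procedures). Sidedness is not stated; two-sided is assumed, and one-sided is tried below.

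**Formula.** For two means with equal groups, n per group = 2 × (1.960 + 0.842)² × (SD/difference)² = 15.70 × (SD/difference)².

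**Attempt to reproduce 62 from the printed inputs (SD 0.10).**

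| Reading of 10 points | Difference in SD | n per group |
|---|---|---|
| 10 | 100 | 15.70 × 0.01² = 0.0016, so trivially 1 |
| 0.10 | 1 | 15.70 × 1 = 15.7 (t-test 16.7), so 16 to 17 |
| 0.010 | 0.1 | 15.70 × 100 = about 1,570 |

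None gives 62. If the difference were 0.10, power at 62 per group would be 99.98%, not 80%.

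**Other routes to 62 for a difference of 0.10.**

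- One-sided 5%: 13 per group.
- Mann–Whitney in place of the t-test: 16/0.955 gives 17; at the lower bound on efficiency, 16/0.864 gives 19.
- Change-score SD of √2 × 0.10 = 0.141: 32.
- Bonferroni for three primary outcomes (alpha 0.05/3): 21.
- The last three stacked: 21 × 2/0.864 = 48.6, still short of 62.
- An unstated clustering allowance: the design effect would have to be 62/15.7 = 3.95. With groups of 10 (Intervention section), that implies an intracluster correlation of (3.95 − 1)/(10 − 1) = 0.33. The sample-size text mentions no such allowance.
- Dropout is added after the 62, so it cannot explain it.

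**Working backwards from 62.** The difference/SD ratio is (1.960 + 0.842) × √(2/62) = 0.503. That fits several pairs:

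- SD 0.10 with a difference of 0.0503 (0.0507 by t-test);
- a difference of 0.10 with an SD of 0.10/0.503 = 0.199;
- a difference of 10 with an SD of 10/0.503 = 19.9.

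**The nearest round value at SD 0.10.** A difference of 0.05 gives 15.70 × 4 = 62.8 (t-test 63.8), so 63 to 64 per group. Power at 62 is 79.5% by the normal approximation and 78.9% by t-test; at 64 the t-test gives 80.1%.

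**Dropout step.** 62/(1 − 0.20) = 77.5, so 78 per group and 156 in total, rounded up to 160. In reverse, 80 × 0.80 = 64 per group.

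**The case against.** The strongest objection is to a firmer claim than the arithmetic allows. A reader might infer that the trial's true target is 0.05 and that the word 10-point is the misprint. The documents do not support this as fact. Only the ratio of about 0.5 is fixed. The SD of 0.10 appears once, without a source or a second value to check it against, and a difference of 0.10 with an SD of about 0.20 would fit 62 just as well. Nor does 0.05 reproduce 62 exactly: it needs 63 or 64. Writing in 0.05 without checking could record a target the trial was never designed for. This objection stands, and the conclusion below is limited accordingly.

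It can also be said that the practical damage is small: 62, 20% and 160 agree with each other, and no design feature or analysis changes. That is true, and it limits the remedy to wording. It does not remove the contradiction, which sits in the trial's only power statement.

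Finally, a journal article may leave detail to a fuller protocol or analysis plan. That covers the sidedness of the test and whether the SD refers to change or to follow-up scores; neither is part of this point, and neither rescues the 10-point figure. It does not cover a set of inputs that are printed and disagree.

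**Conclusion.** The sample-size statement is wrong as written. With SD 0.10, 5% alpha and 80% power, 62 per group matches no reading of a 10-point difference: the candidates need 1, 16 to 17, or about 1,570 per group. The number 62 belongs to a difference of about half an SD, or about 0.05 on the condition that SD 0.10 is right. Which of the two inputs is misprinted cannot be settled from the document.

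A reader might also infer that the trial is the wrong size. The document does not support that: 62 leads coherently to 160, and 80 per group less 20% leaves 64, which gives 80.1% power for half an SD. The fault lies in the stated effect or its scale, not in the total. These results assume a two-sided comparison of two means with equal groups; none of the variants tried brings a difference of 0.10 to 62.

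**What to change.** Check the original calculation, then restate the target difference and the SD on the same 15D scale so that together they reproduce the stated number per group.

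- If SD 0.10 is confirmed, replace the 10-point wording with a between-group difference of 0.05 (0.5 SD) and give 63 to 64 evaluable patients per group in place of 62.
- If the SD is the misprint, correct the SD and give the difference in the same units.

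The cost is one sentence, and the total of 160 stays. The Trial status section says recruitment is open, so the correction can be made before results could influence the choice of target.

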We aim for a total of 160 couples to be randomized in two groups: group rehabilitation as the intervention and normal care as the control group. Participating couples are assessed by two study nurses three times over nine months: at baseline, three, and nine months. Use of health services, institutionalizations and mortality of both patients and caregivers will be retrieved from the central registers until 24 months from the baseline measurements. The flow chart of the study is presented in Figure
1, and the study assessment procedures are described in Table
1.

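### The stated between-arm tests (ANOVA or Mann–Whitney U, chosen by distribution) use no baseline or batch adjustment; a pre-specified baseline- and batch-adjusted linear model would be more precise for very little cost

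*Protocol article*

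**What the plan says.** **Tests.** Under Statistical analyses, for normally distributed variables "statistical comparisons between the groups will be made by using an analysis of variance". Otherwise, "If the variables have a non-normal distribution or ordinal level, statistical comparison between groups will be made using the Mann–Whitney U test". No baseline covariate or randomisation factor is attached to either, and no other test is given for 15D, RAND-36 or SCQ.

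**Scope.** The sentence just before this rule concerns baseline description: "In baseline findings, the continuous variables and descriptive values will be expressed by means with standard deviations (SD) and medians with range". The rule is therefore not tied explicitly to the outcomes, although nothing else in the section would cover them.

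**Outcomes.** Under Outcome measurements, "Primary outcome measures are changes in patients’ HRQoL assessed by 15D", and likewise changes in caregivers' RAND-36 and SCQ.

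**Baseline data.** Under Study procedures, "Participating couples are assessed by two study nurses three times over nine months: at baseline, three, and nine months". Table 1 lists all three primary scales at each of these visits.

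**Randomisation.** "The couples are randomized in clusters of 20", with half allocated to each arm. A target of 160 couples gives 160/20 = 8 batches. An exact 10:10 split within each batch is inferred from the batch size, the equal allocation and the treatment groups of ten.

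**Missing data.** LOCF and worst-rank scoring are both named.

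**The concern.** Comparing mean changes between arms fixes the slope of follow-up on baseline at 1. When the true slope is lower, subtraction adds noise from the baseline measurement, and a chance baseline gap between arms is over-corrected. ANCOVA estimates the slope instead. The baseline scores are already collected, so the precision is available and unused.

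Batch is a feature of the design. If it is balanced across arms and related to outcome, a test that omits it uses too large a standard error.

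The choice between ANOVA and Mann–Whitney U also turns partly on distribution, so the three primary outcomes could be judged by different tests. A Mann–Whitney result gives no mean 15D difference to set beside the planning difference.

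At stake are precision in a trial of 160 couples with 20% expected dropout, and a primary analysis that is fixed beforehand.

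**Working it through.** **1. The plan's own figure.** Inputs from Statistical analyses: SD 0.10, type I error 5% (two-sided assumed), power 80%, 62 per group. n per group = 2(1.960 + 0.842)² × (SD/difference)² = 15.70 × (SD/difference)².

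- Difference 0.10: 15.70, so 16 per group.
- Difference 0.05: 15.70 × 4 = 62.8, so 63 per group. With 62, power is 79.5%.
- Difference implied by 62 per group: 2.802 × 0.10 × √(2/62) = 0.0503.

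The 62 therefore corresponds to a difference of about 0.05. The article's wording of that difference as 10 points is a separate matter; the relative results below do not depend on it.

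**2. Change score against ANCOVA.** Let the score have SD s at both visits, with correlation r (assumed; not in the article).

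- Variance of the change: 2(1−r)s².
- ANCOVA residual variance: (1−r²)s².
- Ratio: (1−r²)/[2(1−r)] = (1+r)/2, which is below 1 for every r < 1.

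| r | variance ratio | variance saved | detectable difference multiplied by √ratio | reduction |
|---|---|---|---|---|
| 0.5 | 0.75 | 25% | 0.866 | 13% |
| 0.7 | 0.85 | 15% | 0.922 | 8% |
| 0.8 | 0.90 | 10% | 0.949 | 5% |

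**3. What this means at the planned size.** The article does not say whether 0.10 is the SD of the change or of the score, so both are shown for a difference of 0.05.

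| r | SD of change = 0.10: n per arm, change → ANCOVA | power at 62, change → ANCOVA | SD of score = 0.10: n per arm, change → ANCOVA | power at 62, change → ANCOVA |
|---|---|---|---|---|
| 0.5 | 63 → 48 | 79.5% → 89.5% | 63 → 48 | 79.5% → 89.5% |
| 0.7 | 63 → 54 | 79.5% → 85.5% | 38 → 33 | 94.9% → 97.4% |
| 0.8 | 63 → 57 | 79.5% → 83.5% | 26 → 23 | 99.3% → 99.6% |

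**4. Cost in degrees of freedom.** One for baseline and seven for 8 batches: 122 − 8 = 114 at 62 per arm. By the noncentral t, with the residual SD held at 0.10, power moves from 78.87% to 78.83%.

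**5. Batch.** Assume, for illustration only, a batch effect on the follow-up score with SD 0.3s, and r = 0.7. The change then has within-batch variance 2(0.3)s² = 0.60s², and about 0.60s² + 0.09s² = 0.69s² when batch is ignored. With batches balanced across arms, the estimate really varies according to 0.60s². The unadjusted test therefore behaves as if its critical value were 1.96 × √(0.69/0.60) = 2.10, a true error of about 3.6%. Simulation (8 batches, 64 per arm, 2,000 runs) gave 3.6% unadjusted and 4.9% for batch-adjusted ANCOVA, with power of 93.9% and 97.3% for a true effect of 0.5s. A batch shift common to baseline and follow-up would cancel from the change.

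**6. Choosing the test by distribution.** With normal data and no batch effect, a normality pre-test followed by ANOVA or Mann–Whitney U had type I error of 4.95% to 5.7% over r = 0.3 to 0.8. Monte Carlo error is √(0.05 × 0.95/2000) = 0.5 points, so no inflation was seen.

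**The case against.** **Scope.** The test rule follows a sentence about baseline findings, this is a condensed article, and covariates are often left to an analysis plan that is not shown. This is fair as a limit on wording: the absence of a covariate list is no fault. The point is that the article does name a between-group method, the only one that could apply to the primary changes, and a better one is available.

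**Baseline is already used.** A reader might infer that the plan ignores baseline altogether and claim a variance saving of 1 − (1−r²) = r², that is 25% to 64% at r = 0.5 to 0.8. The document does not support this: the outcomes are defined as changes, so a follow-up-only analysis is not the comparator. The relevant saving is (1−r)/2.

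**Validity.** A reader might also infer that the standard errors are wrong in general, or that choosing the test by distribution inflates type I error. Neither is shown. The batch effect is not given in the article and, where present, makes the test conservative. Over-correction of a chance baseline gap is not bias over repeated randomisation. Ordinal level is a property of the scale and known beforehand, so only the normality part of the rule can depend on the data.

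**Heterogeneity.** The Discussion's remark about various stages of dementia might be read as a warning of baseline imbalance. In context it concerns whether the scales are suitable and sensitive to change, and it supports nothing about imbalance between arms.

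**Worst ranks.** A worst rank has no numeric 15D value, so a linear model cannot take it directly. This objection stands, and the fix must keep a rank-based analysis.

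**Conclusion.** The point holds as one of efficiency and pre-specification. Adjusting for baseline reduces the variance of the primary comparisons by (1−r)/2: 10% to 25% at an assumed r of 0.5 to 0.8, or a detectable difference about 5% to 13% smaller. The exact ratio rests on equal SDs at the two visits and on a correlation that the article does not state. The further gain from a batch term cannot be sized from the document, and may be nil if batches do not differ.

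The change is worth making because the data are already collected, but the stated analysis is not invalid. Nor is the adjustment entirely free, given the worst-rank rule. Clustering within the intervention groups of ten is a separate issue, and batch terms do not resolve it.

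**What to change.** For each continuous primary outcome, pre-specify one linear model of the follow-up score on arm, the baseline value of the same score and randomisation batch (8 levels). Using the change as the dependent variable with the same terms gives the identical arm effect. Use this model whatever the observed distribution, with robust or bootstrap intervals if residuals are skewed. The article already plans bootstrap intervals for costs, so the technique is within its own methods.

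Keep a rank-based analysis, such as Mann–Whitney U, for the worst-rank scoring and for ordinal scales. State in advance which outcomes it covers and how its result stands beside the linear model.

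The cost is about 8 degrees of freedom (some 0.04 percentage points of power), one additional rank-based analysis for worst-rank cases, and revised analysis wording. No new data are needed.
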